### 3. STUDY DESIGN

#### 3.1. Study design

The study will be conducted in a double-blind crossover design with four randomly sequenced experimental conditions. This 2x2 latin square design will be applied to give a complete picture of the combined effects of capsaicin supplementation and energy balance.

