#### 3.2. Intervention

Subjects will stay for four conditions in a respiration chamber for 36h, twice receiving an energy-balanced (100 En%) diet and twice an energy-restricted (75 En%) diet, both with and without added capsaicin (100%Control, 75%Control, 100%CAPS, 75%CAPS). The four test sessions will be conducted four weeks apart to prevent possible treatment-induced effects and to take eventual effects of menstrual cycle phase on energy intake and energy expenditure in women into account.

Two days prior to each test session subjects will be provided with a diet at home, in energy balance and with the same macronutrient composition as they will receive during the test sessions. On each of the four test days subjects arrive at the University after an overnight fast at 8:00h, whereafter they enter the respiration chamber at 8:30h. Energy expenditure, substrate oxidation and activity level will be continuously measured from 8:30h to 20:30h on the next day. Breakfast will be provided at 8:30h and will consist of wholegrain bread with low-fat margarine, liver paste and strawberry jam, and chocolate milk. At 13:30h subjects will receive lunch, which will consist of wholegrain bread with low-fat margarine, liver paste and meatloaf, ginger cake, low-fat milk, apple and raisin biscuits. Dinner at 18:30h will consist of mixed salad with dressing, vegetable lasagne, low-fat yoghurt and low-fat milk. As part of each meal subjects will consume tomato juice (100%Control, 75%Control conditions) or tomato juice with added capsaicin (100%CAPS, 75%CAPS conditions). Subjects will be instructed to go to sleep around 23:30h. The next morning, subjects will be waked at 7:30h. Thereafter, the same protocol as during the previous day will be followed, until dinner. At 18:30h the subjects will receive an *ad libitum* meal, consisting of iceberg lettuce with cucumber, tomato and dressing, macaroni Bolognese, a dessert and orange juice.

Appetite profile will be measured using anchored 100-mm visual analogue scales (VAS). These questionnaires will be completed every waking hour, and before and after every meal on feelings of hunger, fullness, appetite, satiety, thirst, prospective food consumption, and desire to eat. Mood and anxiety levels will be measured by Profile of Mood State (POMS) (22) and State-trait Anxiety Inventory (STAI) (23) questionnaires at the same time points.

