### 6.2. Randomisation, blinding and treatment allocation

The study will be conducted in a double-blinded crossover design with four randomly sequenced experimental conditions.

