**6.5. Replacement of individual subjects after withdrawal**

New subjects will replace subjects that are withdrawn from the study.

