## **8. STATISTICAL ANALYSIS**

### **8.1. Descriptive statistics**

Data will be presented as means  $\pm$  standard error of the mean (SEM). Energy expenditure will be expressed as total 36h energy expenditure, as well as for the different components (SMR, DIT and AEE). Substrate oxidation will be calculated as carbohydrate, fat and protein oxidation and as RQ. Total energy and macronutrient intake will be calculated to subsequently calculate energy and macronutrient balance. VAS ratings and POMS and STAI scores will be described. Area under the curve (AUC) and area above the curve (AAC) will be calculated using the trapezoidal method for all the variables described above.

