### **8.2. Univariate analysis**

The Statistical Package for the Social Sciences (SPSS) will be used to perform univariate analyses. ANOVA repeated measures will be performed to determine possible differences in energy expenditure and its components, substrate oxidation, *ad libitum* energy intake, energy and macronutrient balance, appetite profiles and mood scores between the four conditions. Multiple linear regression analyses will be performed to determine the independent contribution of gender, age, and factors describing body composition and body fat distribution on the dependent variables. All statistical tests will be two-sided and differences will be considered statistical significant if  $p < .05$ .

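### The '2x2 latin square' label does not fit four conditions in four sessions; no balanced set of orders is given, and the named ANOVA has no period term

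*Protocol*

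**What the plan says.** - **Design (section 3.1).** After announcing a crossover with four conditions in random sequence, the protocol states: "This 2x2 latin square design will be applied to give a complete picture of the combined effects of capsaicin supplementation and energy balance".
- **Conditions and sessions (sections 2 and 3.2).** Two energy levels, each with and without capsaicin, give four conditions. Each has its own chamber stay: "The four test sessions will be conducted four weeks apart to prevent possible treatment-induced effects".
- **Allocation (section 6.2).** The section consists of one sentence: "The study will be conducted in a double-blinded crossover design with four randomly sequenced experimental conditions". It lists no sequences, block or balance rule.
- **Analysis (section 8.2).** "ANOVA repeated measures will be performed to determine possible differences in energy expenditure and its components", across the four conditions, in SPSS. No period or sequence term is named. The separate regression names gender, age, body composition and fat distribution.
- **Withdrawals (section 6.5).** "New subjects will replace subjects that are withdrawn from the study". The sequence that a replacement takes is not stated.

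**The concern.** Taken literally, a 2x2 Latin square places two treatments in two periods, so it cannot describe this trial. The two phrases also point to different randomisation lists. A Latin square balances conditions over sessions by construction, whereas unrestricted random ordering does so only on average. Someone preparing the list cannot tell which is meant, and the choice must be made before the first subject enters.

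Each subject is in the study for at least 3 × 4 = 12 weeks. Habituation to the chamber or seasonal change could shift 36h energy expenditure from session to session. If the orders are unbalanced and the model has no period term, that shift becomes noise in the within-subject contrasts. The trial has 16 subjects and aims for 90% power.

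**Working it through.** **Structure.** A Latin square of order k holds k treatments in k periods using k sequences. Here 2 energy levels × 2 capsaicin levels = 4 conditions in 4 sessions, so k = 4. The 2x2 is the factorial structure. Sixteen subjects give 16/4 = 4 per sequence, and 8 men and 8 women give 2 of each.

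**Planning figures (section 4.4).** Difference 480 kJ/36h; SD 550 kJ/36h, used as the SD of the within-subject difference; two-sided 5%; 16 enrolled. The plan's 14 follows from (1.28 + 1.96)² × 550²/480² = 13.78. The printed formula, with its added 2, gives 15.78; that mismatch is a separate matter. Then 14/0.9 = 15.6, so 16. Paired t-test power at n = 16 is 90.3%.

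**Imbalance under unrestricted orders.** For two conditions in one random order, the session difference is ±1, ±2 or ±3 in 6, 4 and 2 of the 12 ordered placements. Its variance is (6×1 + 4×4 + 2×9)/12 = 40/12 = 3.33. Over 16 subjects the mean difference has SD √(3.33/16) = 0.456 sessions. It is 0.5 or more in absolute value in 31% of randomisations and exactly zero in 5%. In a balanced 4x4 square it is always zero.

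**Effect of a session drift.** The protocol gives no drift, so a linear drift of s kJ per session is assumed, over a range.
- The chance shift in a contrast has SD 0.456 × s.
- The SD of the paired difference becomes √(550² + 3.33 s²).
- Simulated power for 480 kJ, n = 16 (3,000 runs without period, 1,500 with):

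| s (kJ/session) | SD of chance shift | SD of difference | No period, random orders (paired) | With period, random orders | With period, balanced square |
|---|---|---|---|---|---|
| 0 | 0 | 550 | 90% | 90% | 93% |
| 50 | 23 | 558 | 90% | 92% | 94% |
| 100 | 46 | 580 | 87% | 90% | 92% |
| 200 | 91 | 660 | 78% | 92% | 93% |
| 300 | 137 | 776 | 64% | 90% | 93% |

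Monte Carlo error is about √(0.9 × 0.1/1500) = 0.8 percentage points in the last two columns, so differences of one or two points down a column are noise.

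**Like-for-like check.** The no-period column is a paired t-test on 15 df, while the period model pools error over all four conditions on 42 df. A no-period ANOVA with pooled error has 64 − 1 − 15 − 3 = 45 df. From the noncentral t with noncentrality 480/(SD/√16), its power is 93%, 92%, 90%, 81% and 68% down the rows. The balanced square with a period term (SD 550, 42 df) gives 93%. About 2 to 4 points of the gap in the table are therefore due to pooling; the rest is due to the period term.

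**Type I error.** Without a period term, under random orders, it is 4.4–5.9% across these drifts, which is nominal within simulation error.

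**Balance alone is not enough.** A balanced square analysed by a paired test without period has 87% power at s = 100 and 75% at s = 200. The square removes the chance shift from the estimate, but the drift still inflates the error, so the period term is needed too.

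**The case against.** Random sequencing can mean randomising subjects to the rows of a Latin square. On that reading the label is a slip, and the imbalance figures do not apply. This stands in part: the figures are conditional on unrestricted orders. The text still does not settle which procedure is meant.

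Model terms are commonly left to a statistical analysis plan, which is not at hand. Section 8.2 does not exclude a period term or two within-subject factors. This also stands: the analysis half of the point is a weakness of the method as named, not a stated error. The sequence list differs, because it cannot be repaired once subjects have been allocated.

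A reader might infer more than the documents support:
- **That session order is confounded with condition.** It is not. Random ordering averages to zero imbalance and keeps the type I error nominal.
- **That the trial exists to test the interaction and will fail to estimate it.** Section 3.1 speaks of combined effects, but the objectives in section 2 are pairwise contrasts, and no model is ruled out.
- **That incomplete subjects are discarded by rule.** That is a property of the standard repeated-measures routine. Section 6.5 replaces withdrawals and section 4.4 allows 10% drop-out, so the numbers are largely protected, although a withdrawn subject's completed sessions might go unused. Nothing in the protocol shows that replacement would select subjects who tolerate the juice.
- **That presenting means with SEM (section 8.1) misstates precision.** It is descriptive; inference comes from section 8.2.

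**Conclusion.** The design label is wrong as written. It conflicts with the description of randomly sequenced conditions, and the protocol does not say how orders are to be balanced. That much rests on the text alone.

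The consequence is a possible loss of precision. It depends on two things the protocol does not give: whether orders are unrestricted, and how large any session effect is. At 50 kJ per session it is trivial. At 200 kJ per session, power falls from about 90% to 78% in the paired test, or from 93% to 81% with pooled error. The power figures also take the plan's SD of 550 as correct and the drift as linear.

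The point is worth acting on because the remedy needs no extra subjects or visits.

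**What to change.** 1. In section 3.1, describe the design as a 2x2 factorial (capsaicin by energy level) in a four-period crossover.
2. In section 6.2, randomise subjects to the four sequences of a balanced 4x4 Williams square, four per sequence (two men and two women). With the treatment codes of section 10.1, one such square is ABDC, BCAD, CDBA, DACB: each condition occurs once per session, and each ordered pair of neighbours occurs once.
3. In section 6.5, state that a replacement takes the withdrawn subject's sequence.
4. In section 8.2, analyse all completed sessions with a linear mixed model: period, capsaicin, energy level and capsaicin-by-energy interaction as fixed effects, subject as random. Report the contrasts of section 2 with 95% confidence intervals.

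The cost is a randomisation list, analysis wording and 3 of the 45 error degrees of freedom.

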#### 3.2. Intervention

Subjects will stay for four conditions in a respiration chamber for 36h, twice receiving an energy-balanced (100 En%) diet and twice an energy-restricted (75 En%) diet, both with and without added capsaicin (100%Control, 75%Control, 100%CAPS, 75%CAPS). The four test sessions will be conducted four weeks apart to prevent possible treatment-induced effects and to take eventual effects of menstrual cycle phase on energy intake and energy expenditure in women into account.

Two days prior to each test session subjects will be provided with a diet at home, in energy balance and with the same macronutrient composition as they will receive during the test sessions. On each of the four test days subjects arrive at the University after an overnight fast at 8:00h, whereafter they enter the respiration chamber at 8:30h. Energy expenditure, substrate oxidation and activity level will be continuously measured from 8:30h to 20:30h on the next day. Breakfast will be provided at 8:30h and will consist of wholegrain bread with low-fat margarine, liver paste and strawberry jam, and chocolate milk. At 13:30h subjects will receive lunch, which will consist of wholegrain bread with low-fat margarine, liver paste and meatloaf, ginger cake, low-fat milk, apple and raisin biscuits. Dinner at 18:30h will consist of mixed salad with dressing, vegetable lasagne, low-fat yoghurt and low-fat milk. As part of each meal subjects will consume tomato juice (100%Control, 75%Control conditions) or tomato juice with added capsaicin (100%CAPS, 75%CAPS conditions). Subjects will be instructed to go to sleep around 23:30h. The next morning, subjects will be waked at 7:30h. Thereafter, the same protocol as during the previous day will be followed, until dinner. At 18:30h the subjects will receive an *ad libitum* meal, consisting of iceberg lettuce with cucumber, tomato and dressing, macaroni Bolognese, a dessert and orange juice.

Appetite profile will be measured using anchored 100-mm visual analogue scales (VAS). These questionnaires will be completed every waking hour, and before and after every meal on feelings of hunger, fullness, appetite, satiety, thirst, prospective food consumption, and desire to eat. Mood and anxiety levels will be measured by Profile of Mood State (POMS) (22) and State-trait Anxiety Inventory (STAI) (23) questionnaires at the same time points.

### 3.3. Flow chart

| Time    | 8:00 | 8:30 | 9:00 | 10:00 | 11:00 | 12:00 | 13:00 | 13:30 | 14:00 | 15:00 | 16:00 | 17:00 | 18:00 | 18:30 | 19:00 | 20:00 | 20:30 | 21:00 | 22:00 | 23:00 |
|---------|------|------|------|-------|-------|-------|-------|-------|-------|-------|-------|-------|-------|-------|-------|-------|-------|-------|-------|-------|
| Arrival | X    |      |      |       |       |       |       |       |       |       |       |       |       |       |       |       |       |       |       |       |
| EE      | >    | >    | >    | >     | >     | >     | >     | >     | >     | >     | >     | >     | >     | >     | >     | >     | >     | >     | >     | >     |
| PA      | >    | >    | >    | >     | >     | >     | >     | >     | >     | >     | >     | >     | >     | >     | >     | >     | >     | >     | >     | >     |
| Meal    | X    |      |      |       |       |       | X     |       |       |       |       |       | X     |       |       |       |       |       |       |       |
| Urine   | X    |      |      |       |       |       |       |       |       |       |       |       |       |       |       |       | X     |       |       |       |
| VAS     | X    | X    | X    | X     | X     | X     | X     | X     | X     | X     | X     | X     | X     | X     | X     | X     |       | X     | X     | X     |
| POMS    | X    | X    | X    | X     | X     | X     | X     | X     | X     | X     | X     | X     | X     | X     | X     | X     |       | X     | X     | X     |
| STAI    | X    | X    | X    | X     | X     | X     | X     | X     | X     | X     | X     | X     | X     | X     | X     | X     |       | X     | X     | X     |

[illegible]

## 4. STUDY POPULATION

### 4.1. Population

Subjects from the student population will be recruited by advertisements on notice boards at the Maastricht University. Healthy, non-smoking, males and females who are normal weight or overweight (BMI) and aged between 18-50 yrs will be recruited for an initial screening, whereafter a total of 16 subjects (8 males and 8 females) will be included in the study. Because of metabolic disturbances, as the reduced ability to oxidize fat, during the development of obesity are expected to influence the effectiveness of capsaicin treatment, both normal weight and overweight subjects will be included in the study to make comparison between these groups possible (24). During the screening, subjects will undergo anthropometric and body composition measurements, and will complete questionnaires related to health, smoking behavior, use of medication, alcohol consumption, physical activity, eating behavior, mood and anxiety.

### 4.2. Inclusion criteria

A total of 16 subjects (8 males and 8 females) with BMI 20-30 kg/m^2 and aged between 18-50 years will be included in the study. All subjects will be healthy, non-smoking, not using a more than moderate amount of alcohol (> 10 consumptions/wk) or caffeine-containing beverages (> 2 cups/d), being weight stable (weight change < 3kg during the last 6 months), dietary unrestrained and not using medication or supplements except for oral contraceptives in women.

### 4.3. Exclusion criteria

Subjects will be excluded if they are not healthy, smoking, using a more than moderate amount of alcohol or caffeine-containing beverages, not being weight stable, dietary restraint, using medication or supplements except for oral contraceptives in women, or if they do not meet the criteria for BMI and age. Pregnant and lactating women, and subjects with allergies for the used food items will also be excluded from participation.

### 4.4. Sample size calculation

The primary endpoint of this study is the change in 36h energy expenditure.

For the sample size calculation the following formula was used:

$$N = 2 + (Z_{1-\beta} + Z_{1-\alpha/2})^2 \times \sigma^2 / (\mu_{75\%CAPS} - \mu_{75\%CONTROL})^2$$

Herein the  $\beta$  was set at 0.10, which results from a power of 0.9. Consequently,  $Z_{0.9} = 1.28$ . For the  $\alpha$  a value of 0.05 was chosen, which resulted in  $Z_{0.975} = 1.96$ .

It is hypothesized that the 25 En% restriction CAPS diet will show a relatively larger 36h energy expenditure compared with the 25 En% restriction control diet. A study by Yoshioka et al. showed that a combination of red pepper and caffeine significantly increased 24h energy expenditure compared to a control condition ( $10190 \pm 1550$  vs.  $9870 \pm 1490$ ,  $p < .05$ ) (7). This corresponds to an increase in 24h energy expenditure of 320 kJ/24h. Therefore, the smallest change in 36h energy expenditure ( $\mu_{75\%CAPS} - \mu_{75\%CONTROL}$ ) was set at  $1.5 \times 320 = 480$  kJ/36h. The standard deviation was set at 550 kJ/36h, based on several studies performed in the same setting to measure energy expenditure with a respiration chamber as will be used in the current study (25, 26).

The calculated sample size will be:

$$N = 2 + (1.28 + 1.96)^2 \times 550^2 / 480^2 = 14 \text{ subjects}$$

Taking a drop-out of 10% into account, 16 subjects will be included in the experiment.

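### The sample-size formula in Section 4.4 evaluates to 15.8 (16 completers), not 14, so the 16 enrolled hold no 10% drop-out allowance

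*Protocol*

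**What the plan says.** Section 4.4 of the protocol sizes the trial on 36h energy expenditure, comparing 75%CAPS with 75%Control.

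- **Error rates.** β "was set at 0.10, which results from a power of 0.9", with a z-value of 1.28. For α, "a value of 0.05 was chosen, which resulted in" a z-value of 1.96. Section 8.2 agrees on sidedness: "All statistical tests will be two-sided".
- **Effect.** 480 kJ/36h, obtained as 1.5 × 320 kJ/24h.
- **SD.** "The standard deviation was set at 550 kJ/36h", with two cited chamber studies as the source. The section does not say whether this is the SD of a within-subject difference or of a single condition.
- **Result.** "N = 2 + (1.28 + 1.96)^2 \times 550^2 / 480^2 = 14 \text{ subjects".
- **Enrolment.** "Taking a drop-out of 10% into account, 16 subjects will be included in the experiment".

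Sections 4.1 and 4.2 repeat the total of 16 (8 men and 8 women). Section 3.1 describes a "double-blind crossover design with four randomly sequenced experimental conditions", so every subject contributes to the comparison. On attrition, Section 6.5 adds: "New subjects will replace subjects that are withdrawn from the study".

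**The concern.** The leading 2 appears in both the symbolic and the numerical line of the formula, yet the reported result looks like the value without it. If so, the protocol understates the number of completers its own method requires. The two subjects presented as the drop-out margin would then be the two that the formula already asks for.

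At stake is the justification for the trial's size on its primary endpoint. A reader of Section 4.4 would conclude that 14 completers meet the 90% power target and that two losses can be absorbed. By the printed formula, neither follows.

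**Working it through.** **Inputs (all from Section 4.4):** z-values 1.28 and 1.96; SD 550 kJ/36h; difference 480 kJ/36h; drop-out 10%.

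**1. The plan's figure.**

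- (1.28 + 1.96)² = 3.24² = 10.4976
- 550²/480² = 1.3129
- Product = 13.78
- Adding the leading 2: 15.78, rounded up to **16**

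The product alone, 13.78, rounds up to 14, which is the reported figure. Other routes to 14 do not fit the stated inputs. Unrounded z-values give 13.80 without the 2 and 15.80 with it. A one-sided α of 0.05 with the 2 gives 13.24, so 14, but the protocol prints 1.96 and specifies two-sided tests. Power of 80% with the 2 gives 12.31.

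**2. The drop-out step.**

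- As the plan appears to have done it: 14/0.9 = 15.6, so 16.
- From the correct base: 16/0.9 = 17.8, so **18**.

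**3. Power by number of completers.** This takes 550 kJ/36h as the SD of the within-subject difference, which is how the formula uses it. The noncentrality is (480/550) × √n and the test is two-sided at 0.05. Two error terms are shown, because Section 8.2 names repeated-measures ANOVA across four conditions without saying which error term serves this contrast:

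| Completers | Paired t, df = n − 1 | Pooled ANOVA error, df = 3(n − 1), sphericity assumed |
|---|---|---|
| 16 | 0.903 | 0.927 |
| 15 | 0.881 | 0.910 |
| 14 | 0.855 | 0.890 |

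On the paired t-test, the difference detectable with 90% power at 14 completers is 516 kJ/36h, against the planned 480.

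The paired-t column also suggests what the leading 2 is for. At 14 completers the normal approximation gives 0.904 and the t-test 0.855; at 16 the t-test gives 0.903. The term behaves like a small-sample correction for using t instead of z. That is an inference, as the protocol does not explain it.

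**4. Sensitivity to the meaning of the SD.** If 550 kJ/36h is instead the SD within one condition, the SD of the difference is 550 × √(2(1 − r)), where r is the within-subject correlation. Paired-t power at 14 completers is then:

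| r | Power at n = 14 |
|---|---|
| 0 | 0.57 |
| 0.5 | 0.855 |
| 0.6 | 0.921 |
| 0.7 | 0.973 |

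The protocol gives no value of r, so these are illustrations. At r = 0.5 the two readings of the SD coincide.

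**The case against.** The case for leaving this alone is that the trial enrols 16, which is exactly what the correctly evaluated formula requires, and that Section 6.5 replaces withdrawn subjects, so a loss need not reduce the number of completers. This stands, and it limits the consequence. It does not make the printed sum true, nor the statement that 16 includes a drop-out allowance.

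A reader might infer that the 90% target fails as soon as anyone drops out. The documents do not support that. Replacement can restore 16 completers. Even one unreplaced loss leaves 0.881 by the paired t-test, about two points short, and 0.910 with the pooled ANOVA error, which is still above target. The clearer shortfall is at 14 completers without replacement.

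A reader might also infer that the protocol contradicts itself by both inflating for drop-out and replacing withdrawals. It does not: the two measures can coexist, and neither section excludes the other.

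Finally, the power figures depend on reading 550 kJ/36h as the SD of the paired difference. The spread over plausible correlations in step 4 is larger than the effect of two subjects. That is a fair limit on any single power value, but the arithmetic in steps 1 and 2 does not depend on it.

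**Conclusion.** Wrong as written. The printed formula gives 15.8, so 16 completing subjects, and the reported 14 omits the formula's own leading 2. The 16 enrolled therefore contains no 10% drop-out allowance; 18 would be needed to keep one. These statements need only the printed inputs.

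The effect on power is modest and conditional. If 550 kJ/36h is the SD of the within-subject difference and losses are not replaced, power at 14 to 15 completers is 0.855 to 0.881 by the paired t-test, or about 0.89 to 0.91 with the pooled ANOVA error under sphericity. If withdrawals are replaced as Section 6.5 provides, 16 completers give 0.90 to 0.93 on the same assumption.

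This should be fixed because it is a false figure in the primary-endpoint justification. It is not more serious than that, because the number enrolled does not change.

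**What to change.** In Section 4.4:

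- Replace the result of 14 subjects by 15.8, i.e. 16 completing subjects.
- Delete the statement that 16 already takes a 10% drop-out into account.
- State that 16 completers are to be reached through the replacement rule in Section 6.5.
- Say what the 550 kJ/36h SD refers to (a within-subject difference or a single condition, and in the latter case the correlation assumed), and give the power at 14 and 15 completers under that stated assumption and the chosen error term.

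If the sponsor prefers to keep an explicit 10% allowance, the alternative is to enrol 18 and to amend the totals in the Summary and Sections 4.1, 4.2 and 4.4.

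The first route costs only wording: no endpoint, analysis or enrolment beyond the replacement already planned is affected. The stated justification becomes slightly less favourable. The second route costs two more subjects, each with four 36h chamber stays.
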